#### Data Collection

Quantitative data collection was carried out through self-administered questionnaires. The outcome variables were measured at 5 time points: at baseline (T_0_), immediately after the online training (T_1_), a month after training and before information sharing via WhatsApp (T_2_), a month after the start of WhatsApp information sharing (T_3_), and two months after WhatsApp intervention or at the end of intervention (T_4_). All participants in the intervention and control groups were asked to simultaneously fill out digital questionnaires (Google Forms) at a particular time determined by the researcher. Instructions for filling out the questionnaire were listed at the beginning of each questionnaire section to prevent incorrect or incomplete responses. Reminders via SMS and WhatsApp were sent to participants to ensure that the questionnaire was filled. There was no specific data monitoring committee established in this study due to the limited study scale and available resources. Data monitoring was undertaken by an appointed member of the research team (author [name]).

#### Questionnaires

The instrument used to collect the quantitative data was a self-administered questionnaire. The same questionnaire was utilized for both the pretest and posttest and consisted of 7 sections: sociodemographic and job characteristics, attitude, subjective norms, perceived behavioral control, actual behavioral control, role identity, and behavioral intention.

The statements in the questionnaire to measure outcome variables were developed based on an integration of TPB and identity theory as well as the results of the qualitative strand. Alternative responses for each statement were presented on a 7-point Likert scale ranging from strongly disagree to strongly agree. Meanwhile, the actual behavioral control was measured using questions related to knowledge regarding prevention and first aid of travel-related health problems, with “right,” “wrong,” and “do not know” options.

#### Data Management and Analysis

Quantitative data were extracted from the digital questionnaires and transferred to the database. Coding was done to the extracted data, and data values were checked by two data analysts. Data without participants’ names were exported into a file format suitable for analysis with statistical software. The electronic data were stored on a computer protected with a password and only accessible to the research team.

Quantitative data will be analyzed descriptively by calculating the frequency distribution for categorical data as well as the total scores, mean, median, standard deviation, and range of minimum to maximum scores on numerical data. The comparability of the intervention group and the control group in terms of control variables will be analyzed using the chi-square test for categorical data and independent *t* test or Mann-Whitney *U* test for numerical data [39-41]. Data normality will be calculated using Kolmogorov-Smirnov test. Additionally, data homogeneity will be tested using the Levene test [39,42]. A complete case analysis will be performed to handle missing outcome data.

The mean comparison test will be conducted to determine mean differences between the intervention and the comparison groups. Repeated measures analysis of covariance (ANCOVA) will be employed because the measurement of dependent variables was conducted repeatedly at 5 time points, and there are covariates that need to be controlled in the analysis [39].

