**Methods:**

This is an exploratory sequential mixed methods research. The first phase consisted of a qualitative study with an informed grounded theory design. In-depth interviews were carried out with tour guides from all language divisions and policymakers of the Indonesian Tour Guide Association Bali Branch or Himpunan Pramuwisata Indonesia Daerah Bali (HPI Bali). The interview guidelines were developed based on the theory of planned behavior and identity theory. Qualitative data were analyzed thematically. In the interim phase, a travel health education model and questionnaire were developed based on the qualitative findings. The initial model and its instruments were finetuned after consultation with travel medicine and health promotion experts. Furthermore, the validity and reliability of the questionnaire were tested on 30 tour guides. The second phase consisted of a quantitative study with a randomized pretest-posttest control group design. A total of 76 tour guides in the intervention group received comprehensive travel health education, while 76 in the control group received no specific intervention. Outcome variables (ie, attitudes, subjective norms, perceived behavioral control, actual behavioral control, role identity, and behavioral intention) were measured at baseline (T_0_), after the online training (T_1_), before information sharing via WhatsApp (T_2_), a month after the start of the WhatsApp intervention (T_3_), and at the end of the WhatsApp intervention (T_4_). The mean difference of each outcome variable before and after the intervention will be compared between the intervention and control groups. Thereafter, the quantitative and qualitative findings will be integrated into a joint display.

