#### Participants

The minimum sample size in this study was calculated by employing the WHO Sample Size Determination software using the formula of a 1-tailed hypothesis test for a difference in two population means [37]. Using the parameters *d*=10.0, µ1=71.2, µ2=66.2, α=.05, and 1–β= 90% and taking into account a dropout rate of 10%, the minimum number of samples for each intervention and control group was 76. Sample selection was carried out with disproportionate stratified random sampling from the list of tour guides who were HPI Bali members. The selected tour guides were contacted to determine if they met the eligibility criteria. Those who did were given a further explanation of the research and asked to sign the informed consent form if they were willing to participate.

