#### Study Outcomes

The outcomes of this study referred to the constructs of integrated TPB and identity theory, including attitude, subjective norms, perceived behavioral control, actual behavioral control, behavioral intention, and role identity. A summary of the outcomes is presented in Table 1.

In addition to those outcome variables, several variables were controlled by analysis, namely age, sex, education, length of work, employment status, tourists’ country of origin, and type of tourism activities.

**Table 1 table1:** Summary of study outcomes.

Study outcomes	Definition	Data measurement and analysis scale	Data source (time point)
Attitude	Psychological tendencies expressed by the tour guides regarding providing travel health information to tourists	Measurement scale: ordinal (Likert scale) Data analysis scale: interval	Self-administered questionnaire (T_0_, T_1_, T_2,_ T_3,_ T_4_)
Subjective norms	Tour guides’ perception of the extent to which providing travel health information to tourists is something that is expected by the tourists they serve, their employers (travel agents), HPI^a^, and the community	Measurement scale: ordinal (Likert scale) Data analysis scale: interval	Self-administered questionnaire (T_0_, T_1_, T_2,_ T_3,_ T_4_)
Perceived behavioral control	Tour guides' confidence in their ability to provide travel health information to tourists	Measurement scale: ordinal (Likert scale) Data analysis scale: interval	Self-administered questionnaire (T_0_, T_1_, T_2,_ T_3,_ T_4_)
Actual behavioral control	Tour guides’ knowledge regarding the prevention and first aid of travel health problems	Measurement scale: ordinal (Likert scale) Data analysis scale: interval	Self-administered questionnaire (T_0_, T_1_, T_2,_ T_3,_ T_4_)
Role identity	Tour guides’ perception of the extent to which travel health promotion is a part of their role	Measurement scale: ordinal (Likert scale) Data analysis scale: interval	Self-administered questionnaire (T_0_, T_1_, T_2,_ T_3,_ T_4_)
Behavioral intention	Tour guides’ willingness to provide travel health information to the tourists they serve	Measurement scale: ordinal (Likert scale) Data analysis scale: interval	Self-administered questionnaire (T_0_, T_1_, T_2,_ T_3,_ T_4_)

^a^HPI: Himpunan Pramuwisata Indonesia (Indonesian Tour Guide Association).

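### The pre-intervention score (T0) is treated as a fifth outcome level instead of a covariate, and the tested term is not named; adjusting for T0 would be a free gain

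*Protocol article*

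**What the plan says.** Under Data Collection the protocol article states "The outcome variables were measured at 5 time points: at baseline (T_0", followed by T1 to T4. Table 1 lists T0 to T4 as the data source for each of the six outcomes. T0 precedes any training.

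Under Data Management and Analysis the model is chosen on this ground: "Repeated measures analysis of covariance (ANCOVA) will be employed because the measurement of dependent variables was conducted repeatedly at 5 time points". The other reason given is that covariates need control. The same paragraph describes the aim as finding mean differences between the two groups.

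The covariates are named under Study Outcomes: "several variables were controlled by analysis, namely age, sex, education, length of work, employment status", and then the tourists' country of origin and the type of tourism activities. That makes seven, and the T0 score of the outcome is not one of them.

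The Methods part of the abstract describes the comparison differently: "The mean difference of each outcome variable before and after the intervention will be compared between the intervention and control groups".

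**The concern.** In a randomised pretest-posttest trial the true group difference at T0 is zero. T0 tells us nothing about the effect, but it predicts the later scores. As an outcome level it either pulls down an averaged group effect or has to be removed again through an interaction or a change score. As a covariate it removes residual variance and leaves the effect intact.

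The wording also leaves the tested term open. A mean difference between groups most naturally suggests the group main effect. A before-after difference suggests change from T0 or group-by-time. These do not estimate the same quantity. This is the only efficacy model described, and it serves six outcomes, so a reader should be able to tell which estimate will be reported.

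**Working it through.** **Inputs from the article (Participants).** The formula is the "formula of a 1-tailed hypothesis test for a difference in two population means", with "µ1=71.2, µ2=66.2", so the difference is 71.2 − 66.2 = 5.0. The value 10.0 is printed as d; I read it as the SD because that reproduces the stated size. Alpha is 0.05, power 90%, dropout 10%. The Discussion reports full participation, so I use 76 per arm.

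**The plan's own figure.** n = 2 × [10 × (1.645 + 1.282)/5]² = 68.5, so 69 per arm, and 69 × 1.10 = 75.9, so 76. This agrees with "the minimum number of samples for each intervention and control group was 76". (Dividing by 0.90 gives 77.) The sample size is not in dispute. With 76 per arm the planned one-sided two-mean test has 92.5% power.

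**Assumptions not in the documents.** The correlation ρ is equal between all pairs of time points, and the effect is 5 points at each of T1 to T4.

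**What each test estimates.**
- Group main effect over five levels: (0 + 5 + 5 + 5 + 5)/5 = 4.0. For any pattern of later effects it is 4/5 = 0.8 of their T1 to T4 average. Simulation with 4,000 runs at each of ρ = 0.3, 0.5 and 0.7 gave 3.99 to 4.00.
- Change from T0, or T1 to T4 adjusted for T0: the full 5.0.
- Group-by-time: an omnibus test on 4 df, with no single estimate.

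**Variances per participant.**
- Five-level mean: 100(1 + 4ρ)/5
- T4 change: 200(1 − ρ)
- T4 adjusted for T0: 100(1 − ρ²)
- T1 to T4 mean minus T0: 100[(1 + 3ρ)/4 + 1 − 2ρ]
- T1 to T4 mean adjusted for T0: 100[(1 + 3ρ)/4 − ρ²]

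For the single-df tests, two-sided 5% power is Φ(difference/√(2V/76) − 1.96). The interaction uses a noncentral F. The effects centred on 4.0 are (−4, 1, 1, 1, 1), with sum of squares 20, so λ = (76/2) × 20/[100(1 − ρ)] = 7.6/(1 − ρ), on 4 and 600 df.

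| Test | ρ = 0.3 | ρ = 0.5 | ρ = 0.7 |
|---|---|---|---|
| Group main effect, T0 to T4 | 96.1% | 88.9% | 80.7% |
| Group-by-time, 4 df | 75.2% | 89.3% | 99.0% |
| T4 change from T0 | 74.1% | 86.9% | 97.8% |
| T4 adjusted for T0 | 89.8% | 94.5% | 99.1% |
| Mean T1 to T4 minus T0 | 90.9% | 97.4% | 99.9% |
| Mean T1 to T4 adjusted for T0 | 99.9% | 99.9% | >99.9% |

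The last row is 99.9% or more, after rounding, at every ρ from 0.2 to 0.8.

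**Adjustment against change score at T4.** The variance ratio is 100(1 − ρ²)/[200(1 − ρ)] = (1 + ρ)/2. Adjustment is therefore 35%, 25% and 15% lower in variance at ρ = 0.3, 0.5 and 0.7.

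**Where T4 adjusted for T0 overtakes the main effect.** Setting 80/(1 + 4ρ) = 25/(1 − ρ²) gives 80ρ² + 100ρ − 55 = 0, so ρ = 0.41. Below that, the five-level main effect has more power than the T4 contrast.

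**Against the planned one-sided test.** The main effect has 98.1%, 93.8% and 88.2% power at ρ = 0.3, 0.5 and 0.7. It falls below 92.5% only when 80/(1 + 4ρ) < 25, that is ρ > 0.55, and below 90% only when ρ exceeds about 0.64.

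**The case against.** A reader might infer that the trial's effect estimate will be diluted by 20%. The documents do not support that without a condition. It follows only if the group main effect over T0 to T4 is the test. The article does not say so, and the abstract's before-after comparison and the pretest-posttest design point to change or group-by-time, where nothing is diluted.

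A reader might also infer that the trial is underpowered. That is not shown either. No correlation is given, and at low to moderate correlation even the diluted test keeps more than 90% one-sided power.

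Further points on the other side are fair. Baseline as a repeated response is a legitimate analysis of a randomised trial, and its group-by-time contrasts are unbiased. A before-after contrast is one degree of freedom within group-by-time, so abstract and analysis section could describe a single model. The intervention is staged, with T1 and T2 before the WhatsApp component, so a constant effect is a convenience. The tested term may be named in a fuller document that is not shown.

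All of this limits the size and seriousness of the point. It does not remove it. T0 is placed on the outcome side and the listed covariates omit it; both are stated choices. For the same endpoint, adjusting for T0 has lower variance than the change score at every correlation below 1.

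**Conclusion.** The point holds as an efficiency and clarity improvement, not as an error that invalidates the analysis. T0 is counted among the five outcome levels, the baseline score is missing from the listed covariates, and the tested term is open between two descriptions. Under the main-effect reading, a constant 5 points becomes 4.0. Under the other readings the estimate is sound but less precise than it could be: at ρ = 0.5, two-sided, 87% for the T4 change score against 94.5% for T4 adjusted for T0, and 89% for the 4-df interaction against 99.9% for the adjusted T1 to T4 mean.

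The power figures rest on compound symmetry, an assumed ρ and a constant effect over T1 to T4. None of these is in the article. The advantage is not uniform across contrasts either: T4 adjusted for T0 has less power than the five-level main effect when ρ is below about 0.4.

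**What to change.** Use T1 to T4 as the repeated outcomes. Add each participant's T0 score on the same scale as a covariate beside the seven listed. Fit group, time and group-by-time, and name one contrast before the group results are examined:

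- the adjusted group difference averaged over T1 to T4, which is the more powerful choice under the assumptions above; or
- the adjusted difference at T4, if the end-of-intervention effect is the question, accepting the lower power at low correlation.

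Report the remaining time-specific differences as supporting. Reword the before-after sentence in the abstract to match.

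The cost is a change of wording and about one degree of freedom per model. T0 is already part of the measurement schedule for all participants, so no new data are needed.

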### Data Integration

Mixed methods research employs various approaches and data collection and analysis methods, which are integrated to answer a research question. Therefore, integration between the qualitative and quantitative approaches during the research process is a defining feature of mixed methods research [43]. The integration procedure in this study will be carried out through the development of joint displays that will demonstrate the relationship between quantitative and qualitative findings [32,43]. The joint display procedure aims to interpret how the results of quantitative research support the quality and the appropriateness of the context and culture of an intervention developed specifically for a particular population [32].

### Ethics Approval

This study received ethical clearance from the Institutional Review Board of the Faculty of Medicine, Udayana University/Sanglah General Hospital (number 1419/UN14.2.2.VII.14/LT/2021). The informed consent procedure was followed, and written consent was provided by the participants. Data obtained throughout the research process were kept confidential and stored in computers and cabinets only accessible to the research team. The participants’ anonymity was upheld by not including their names or other identifiable characters in transcriptions, research reports, or publications.

## Results

Qualitative data collection was conducted from May to June 2021. There were 21 informants including tour guides from 11 language divisions and the head and secretary of HPI Bali. Qualitative findings revealed some negative behavioral, normative, and control beliefs that influenced tour guides’ lack of intention and behavior. Moreover, their role as “nonhealth actors” informed their low intention to provide health information to tourists. A lack of knowledge regarding prevention and first aid of frequent travel-related health problems was also documented.

A comprehensive travel health education model was developed at the interim phase (July to October 2021). The instruments of the model, namely the training module, guidebook, and media for WhatsApp information sharing, were designed based on the qualitative findings. These instruments were further finetuned after consultation with travel medicine and health promotion experts. The questionnaire was also tested for its validity and reliability with 30 tour guides. Refinements to the questionnaire were made according to the results.

The travel health education model includes 10 hours (2 days) of online training via Zoom and weekly travel health information sharing via the WhatsApp group for 2 months. The training content and format were included in the training module (Figure 2). The topics covered in the training included:

The importance of travel health information for touristsThe potential role of tour guides in tourists’ healthAssessment of tourists’ health risksPrevention and first aid of general travel-related health problems, water and foodborne diseases, allergic reactions, respiratory tract infections (including COVID-19), mosquito and other insect bites, rabid animal bites, snake bites, stings and punctures from marine animals, methanol poisoning, sexually transmitted infections, and trauma or injuryHealth and safety hazards of tourist attractions and travel health facilities in BaliCommunication techniques in travel health promotion to tourists

The training materials were delivered by travel medicine, health promotion, and medical emergency experts. Participants also received a travel health guidebook containing information on the prevention and first aid of various travel-related health problems (Figure 2).

WhatsApp information sharing was initiated in December 2021, a month after training. Participants were invited to a WhatsApp group and received weekly travel-related health information for 2 months. Participants asked questions and shared their experiences in the WhatsApp group. A moderator answered the questions and facilitated discussions among the participants. A total of 76 tour guides in the intervention group fully participated from the beginning to the end of the intervention (November 2021 to February 2022). An identical number of tour guides in the control group received no intervention but completed a series of self-administered questionnaires.

**Figure 2 figure2:**
[figure not shown]
Training module and travel health guidebook.

## Discussion

### Initial Findings

This study aims to develop a comprehensive, relevant, and effective travel health education model for tour guides. The model is comprehensive because it addresses all determinants of behavior according to TPB and identity theory. This model is also relevant to tour guides’ needs because it was developed with active participation from tour guides and accommodated their perceptions and preferences. The results of 21 in-depth interviews were used to develop the components of the initial travel health education model. The qualitative results of this mixed methods study confirm the findings of a cross-sectional study on tour guides in Bali showing that improvements should be made in tour guides’ provision of travel health information to tourists [23]. The qualitative data also indicate a need to address the determinants of travel health information provision to tourists, namely tour guides’ attitude, subjective norms, perceived behavioral control, role identity, actual behavioral control, and intention. The education content was developed using information on tour guides' normative beliefs, behavioral beliefs, control beliefs, role identity, and information regarding various health hazards and health problems encountered by tourists throughout their travel.

Tour guides in Bali have limited exposure to information on the prevention and first aid of travel-related health problems. Most of the informants showed a preference for training as a direct and interactive way of obtaining information regarding travel health. Due to the COVID-19 pandemic and its resultant public health measures, online training is more feasible and safer to implement than traditional face-to-face learning. Moreover, online training can be provided to tour guides residing outside Bali. Many tour guides moved back to their hometown during the pandemic because Bali is currently closed for international tourism. Training was complemented with information sharing via WhatsApp to maintain the retention of acquired information and enable further discussion. WhatsApp is considered an appropriate platform for education because it is the main communication platform used in HPI Bali.

Participation in the quantitative study was challenged by the fact that many tour guides have become jobless and are facing economic challenges due to COVID-19. Therefore, the participants were given internet credit and compensated for their time. All participants in the intervention and control groups fully participated in this study. No conclusions regarding the effectiveness of this model could be made because this study is still in the quantitative data analysis phase.

### Comparison to Prior Work

Published literature on interventions to improve the involvement of tourism actors in travel health promotion is still limited. Most of publications so far have been observational studies focusing on the travel health-related knowledge, attitude, and practices of actors in the tourism sector [23,44-47]. There was an experimental study in Canada examining the effectiveness of a health promotion model in the form of providing brochures, pamphlets, and website to improve travel agents’ referral behavior to travel clinics for pretravel consultation [31]. However, a comparison could not be made with this study due to the different target population, targeted behavior changes, and setting.

